### The control

The control condition consists of a waiting list with unrestricted access to TAU. In Sweden, usual care often involves participating in a support group for children of substance abusing parents, frequently provided by the municipalities. Furthermore, there are a few different Swedish websites available providing information and some level of support to this target group. The one with the greatest focus on alcohol within families is the aforementioned Drugsmart website provided by the Swedish Council for Information on Alcohol and Other Drugs. This website contains general information and facts about alcohol and drugs in addition to more specific information and activities for our target group (*e.g*., a live-chat, a "movie-maker", stories). We have reasoned that it is most ethical sound to suggest that the participants in this study, including those allocated to the control condition, visit the Drugsmart website.

### Sample size

This trial is designed to detect a medium or larger effect size, corresponding to a standardized mean difference (Cohen's d) of > 0.5 [43]. An *a priori *calculation of the estimated sample size, using the software G*Power [44] reveals that it is required that a total of 128 participants (64 in each group) enroll in the trial (power = 0.80, α = 0.05, 2-tailed). However, in a pilot study of a web-based intervention aimed at young people having at least one parent diagnosed with a psychiatric or multiple psychological disorders, or an addiction problem, the attrition rate was found to be 28% [26]. Assuming a similar attrition rate of 30%, we therefore need to enroll a minimum of 128/(1-0.3) = 183 participants in the trial.

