**Methods/Design:**

The RCT will include at least 183 adolescents (15-19 year old) who will be randomly allocated to two conditions where one group has access to the web-ICAIP and the other is a waiting list control group. Participants will be recruited from websites containing information and facts for adolescents about alcohol and other drugs. Possible participants will be screened using the short version of the Children of Alcoholics Screening Test (CAST-6). The assessment consists of a baseline and two follow-up measurements taking place after two and six months, respectively. The primary outcomes include the Center for Epidemiological Studies Depression Scale (CES-DC), a coping behavior scale, and also the short version of the Alcohol Use Disorders Identification Test (AUDIT-C). Additional outcomes include the "Ladder of life" which measures overall life satisfaction and questions concerning program adherence.

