### Assessment

A baseline assessment will take place before randomization, and two follow-ups will take place two and six months after the initial assessment. Participants will be invited to each assessment by e-mails and if necessary, up to three reminders will be sent 5, 10, and 15 days after the first invitation. All assessments are online surveys distributed as described above. To enhance response rates, participants will receive an e-mail containing a cinema gift certificate corresponding to 11 Euros as compensation for completing each assessment. If a participant completes all assessments an additional gift certificate will be given. The participant can subsequently receive four cinema gift certificates totaling 44 Euros.

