### Analyses

In addition to per protocol analysis, data will be analyzed according to the intention-to-treat principle, and all randomized participants will subsequently be included irrespective of whether or not they stayed in the trial. Missing data will be handled by applying the technique of multiple imputation using the Missing Value Analysis routine in the SPSS software (IBM SPSS Statistics 20, IBM Corporation).

Data analyses consist of comparing outcome measurements, at the baseline and subsequent follow-up assessments, within groups and between groups. The effects of the web-ICAIP will be estimated using Cohen's d where a value of around 0.2 indicates a small effect size, and values around 0.5 and 0.8 indicate a medium and large effect size, respectively [43].

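### The sample size fits one comparison, but the protocol names three unranked primary outcomes at two unranked follow-ups and does not say which comparison it serves

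*Protocol article*

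**What the plan says.** - **Primary outcomes.** The abstract states: "The primary outcomes include the Center for Epidemiological Studies Depression Scale (CES-DC), a coping behavior scale, and also the short version" of the AUDIT. The Primary outcomes section lists the same three scales and puts none above the others. The research questions under the Objective cover the same three areas: coping, mental health and alcohol.
- **Time points.** The Assessment section says that "two follow-ups will take place two and six months after the initial assessment". Neither is called primary.
- **Sample size.** The target effect is "corresponding to a standardized mean difference (Cohen's d) of > 0.5". The calculation asks for "a total of 128 participants (64 in each group) enroll in the trial (power = 0.80, α = 0.05, 2-tailed"), and then "we therefore need to enroll a minimum of 128/(1-0.3) = 183 participants in the trial". It names no outcome and no time point.
- **Analyses.** "Data analyses consist of comparing outcome measurements, at the baseline and subsequent follow-up assessments, within groups and between groups". Effects are to be expressed as Cohen's d. The section gives no significance level, no order of testing and no success rule.
- **Limitations.** Low power is discussed only in relation to the assumed effect size and attrition.

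**The concern.** A single calculation is offered as the basis for enrolment, while the stated set of primary comparisons has six members (three outcomes at two times). The error rate and power behind enrolment therefore belong to one comparison that is not identified.

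This matters when the results are read. With six primary comparisons and no rule, a favourable result on any one of them could be presented as evidence of efficacy, and 5% would then understate the risk of a false claim. If the claim needs all three outcomes, 80% overstates the chance of success. If alpha is later divided among the outcomes, the stated power no longer applies to each of them.

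**Working it through.** **Inputs.** From the Sample size section: d = 0.5, two-sided alpha 0.05, power 0.80, "64 in each group", attrition 30%. From the outcome and assessment sections: 3 primary outcomes and 2 follow-ups. The protocol gives no correlations between outcomes, between times or with baseline, so those used below are assumptions shown as ranges.

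**1. The plan's own figure.** A two-sample t-test (noncentral t) with d = 0.5, two-sided 0.05 and power 0.80 needs 63.8 per group, rounded up to 64, or 128 in total. Power at 64 per group is 0.801. For attrition, 128/(1 − 0.3) = 182.9, rounded up to 183. Both figures reproduce.

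**2. Any comparison counts, each tested at 5% (an assumed rule).** For k independent tests, the chance of at least one false positive is 1 − 0.95^k.
- k = 3 (one time point): 1 − 0.95³ = 14.3%.
- k = 6 (both time points): 1 − 0.95⁶ = 26.5%.

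Correlation lowers these figures. By simulation, with an assumed between-time correlation of 0.6 for the six tests:

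| Correlation between outcomes | 3 tests | 6 tests |
|---|---|---|
| 0.3 | 13.6% | 23.0% |
| 0.5 | 12.5% | 21.3% |
| 0.7 | 10.9% | 18.5% |

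**3. All three outcomes must succeed at one time point, each at 5%.** If independent, joint power is 0.801³ = 0.51. By simulation (normal approximation) it is about 0.58, 0.62 and 0.67 at outcome correlations of 0.3, 0.5 and 0.7. The approximation runs about one percentage point high: it gives 0.53 under independence.

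**4. Family-wise control over three outcomes at one time point.** The first Holm step uses alpha 0.05/3 = 0.0167.
- Power for one outcome at 64 per group and d = 0.5 is 0.656. Power of 0.80 is reached at d = 0.58.
- If all three effects are 0.5, average per-outcome power under the full Holm procedure is about 0.72 to 0.76 for outcome correlations from 0.9 down to 0.
- To reach 0.80 at the first step without baseline adjustment takes 86 per group, or 172 completers. 172/0.7 = 245.7, so 246 enrolled.

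**5. The same first step with baseline adjustment.** Adjusting for a baseline value with correlation r raises the effective effect to 0.5/√(1 − r²).

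| r (assumed) | Effective d | Power at alpha 0.0167 |
|---|---|---|
| 0.3 | 0.524 | 70% |
| 0.4 | 0.546 | 74% |
| 0.5 | 0.577 | 80% |
| 0.6 | 0.625 | 86% |

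**The case against.** Four counter-arguments deserve weight.

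**No level is stated for the analyses.** A reader might infer that each of the six comparisons will be judged at 5%. The protocol does not say so. The only alpha is in the Sample size section, and the Analyses section speaks of estimating Cohen's d. This stands: the 14.3% and 26.5% describe an assumed decision rule.

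**Some readings keep both figures.** A reader might infer that no reading gives both 5% and 80%. That goes too far. The Objective poses three separate questions. If each is its own claim at one time point, each has alpha 0.05 and power 0.80, and whether separate claims need family-wise control is a debated choice. Under Holm at one time point, with all three effects at 0.5, the chance of at least one success is about 96% for independent outcomes. It is still about 80% at correlation 0.8, and falls to about 76% at stronger correlation. So an at-least-one claim could also keep both figures, provided that all three effects are real. This stands as well, but the protocol adopts none of these readings, and even with separate claims two follow-ups leave two chances per outcome.

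**The sample size is not an arithmetic error.** A reader might infer that 128 or 183 is miscalculated. Both are right for one comparison.

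**An analysis plan may exist.** The multiplicity procedure may properly be left to it, so its absence from a condensed article is not the point here. What remains is a mismatch between two items that the article itself states: the set of primary comparisons and the single comparison used to fix enrolment. Dividing alpha in a later plan would change the power stated for each outcome. Leaving it undivided would leave open what the 5% refers to.

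**Conclusion.** The concern holds as a mismatch between the primary comparisons and the enrolment basis. The 128 completers and 183 enrolled are correct for one comparison, and the protocol does not say which of six that is. Without adjustment, the stated 5% and 80% both apply only if each outcome is a separate claim at a single time point.

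How much is lost depends on the missing rule:
- **Any of three or six comparisons at 5%:** false-positive chance 14.3% or 26.5% if independent. With assumed outcome correlations of 0.3 to 0.7 and between-time correlation 0.6, it is about 11% to 14% or 18% to 23%.
- **All three outcomes at one time point:** power about 51% to 67% for correlations of 0 to 0.7.
- **Holm over three outcomes:** power 66% per outcome at the first step, or about 72% to 76% on average if all three effects are 0.5.

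The single-comparison figures and the independence results are firm. Every correlated or baseline-adjusted figure rests on assumed correlations.

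**What to change.** Before outcome data are seen:

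1. Name one primary time point and make the other secondary. The choice belongs to the sponsor; the documents do not settle it.
2. Then take one of two routes.
   - **One primary outcome.** The other two become secondary, and 128 and 183 stand as written.
   - **Three primary outcomes.** Test them with Holm at a family-wise two-sided 5%, and claim efficacy only for outcomes that pass. Restate power for 128 completers at d = 0.5: 66% per outcome at the first step (80% at d = 0.58), and about 72% to 76% on average if all three effects are 0.5.
3. On the second route, consider adjusting for the baseline value, which is already collected. State the assumed correlation and show a range. First-step power returns to 80% only at a correlation of about 0.5 or more. A reader might infer that no extra enrolment is needed, but the protocol gives no correlation, so that is conditional. Without adjustment, 80% at the first step needs 246 enrolled.

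The cost is a few sentences in the Sample size and Analyses sections. The downside is that, if three primary outcomes are kept, the stated power becomes less favourable unless the baseline correlation is high enough or enrolment rises.

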### Analyses

In addition to per protocol analysis, data will be analyzed according to the intention-to-treat principle, and all randomized participants will subsequently be included irrespective of whether or not they stayed in the trial. Missing data will be handled by applying the technique of multiple imputation using the Missing Value Analysis routine in the SPSS software (IBM SPSS Statistics 20, IBM Corporation).

Data analyses consist of comparing outcome measurements, at the baseline and subsequent follow-up assessments, within groups and between groups. The effects of the web-ICAIP will be estimated using Cohen's d where a value of around 0.2 indicates a small effect size, and values around 0.5 and 0.8 indicate a medium and large effect size, respectively [43].

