### Randomization

After completing the baseline assessment, each participant will be allocated to the intervention or the control group. An unrestricted random allocation sequence will be generated by an external researcher using the Random Allocation Software [41]. Participants will be informed about their allocation by e-mail, and those who are randomized to the treatment group receive a username and password in order to be able to login to the web-ICAIP website. All participants are informed that they have access to all the other content on the Drugsmart website.

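### The analysis as described treats the baseline score as one more time point and names no adjustment for it, so it gives up precision that data already collected would supply

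*Protocol article*

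**What the plan says.** The Analyses section of the protocol article describes the comparison in one sentence: "Data analyses consist of comparing outcome measurements, at the baseline and subsequent follow-up assessments, within groups and between groups". It adds that the effect will be expressed as Cohen's d. It names no test, model or covariate, and it does not say whether d comes from follow-up scores, change scores or adjusted scores.

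Three other sections bear on this:

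- Assessment: "A baseline assessment will take place before randomization". The follow-ups come two and six months later.
- Randomization: "An unrestricted random allocation sequence will be generated by an external researcher". Allocation follows completion of the baseline survey, and no stratification or balancing on baseline scores is described.
- Sample size: the target is a standardised difference, "corresponding to a standardized mean difference (Cohen's d) of > 0.5", with "power = 0.80, α = 0.05, 2-tailed". This gives "a total of 128 participants (64 in each group) enroll in the trial" before attrition. No baseline-to-follow-up correlation enters the calculation.

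**The concern.** Read as a description of what will be done, the analysis sentence makes baseline another occasion on which scores are compared, not a covariate in the follow-up comparison. Neither of the extra comparisons it lists makes up for that. Comparing the arms at baseline does not correct the follow-up difference for any imbalance found. Change within an arm does not estimate the effect of the intervention.

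Two things are at stake. The first is precision: each participant's baseline score predicts part of the follow-up score, and an unadjusted comparison leaves that part in the error term. The second is conditional error: simple randomisation does not balance the baseline scores, so part of a chance difference between arms reappears at follow-up. The article's own limitations section concedes that the study may be under-powered if the effect is smaller or attrition higher than assumed, so free precision has real value here.

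**Working it through.** **Inputs.** From the Sample size section: d = 0.5, two-sided α = 0.05, power 0.80, 64 per group, 30% attrition. Assumed, because the article gives no value: r, the correlation between baseline and follow-up scores, taken as 0.3, 0.5 and 0.7, with equal SDs at the two times and a linear relation.

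**1. The plan's own figures.** Two-sample t-test, noncentrality = d × √(n/2). With n = 64: 0.5 × √32 = 2.83 on 126 df, power 80.1%. With n = 63 the power is 79.5%, so 64 per group is the smallest size that reaches 80%. Attrition: 128/0.7 = 182.9, rounded up to 183. Both figures reproduce, and they are those of a plain two-group comparison.

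**2. Adjusting for baseline (ANCOVA).** Residual variance is multiplied by (1 − r²), so the effective d is 0.5/√(1 − r²), on 2n − 3 = 125 df.

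**3. Change scores, for comparison.** Variance is multiplied by 2(1 − r), so the effective d is 0.5/√(2(1 − r)).

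| r | SE ratio, ANCOVA to unadjusted | Power, unadjusted | Power, ANCOVA | Power, change score | Completers for 80% with ANCOVA | Enrolled at 30% attrition |
|---|---|---|---|---|---|---|
| 0.3 | 0.95 | 80.1% | 83.7% | 66.0% | 118 | 169 |
| 0.5 | 0.87 | 80.1% | 90.0% | 80.1% | 98 | 140 |
| 0.7 | 0.71 | 80.1% | 97.6% | 95.2% | 68 | 98 |

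For example, at r = 0.5, 1 − r² = 0.75 and the effective d is 0.5/0.866 = 0.577. The noncentrality is 0.577 × √32 = 3.27, which gives 90.0%. Put another way, 128 completers analysed with adjustment are worth about 128/0.75 = 171 analysed without it.

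**4. Chance imbalance.** With 64 per arm, the difference between arms in mean baseline score has SD √(2/64) = 0.177 baseline SDs, so its 95% range is ±1.96 × 0.177 = ±0.35. At r = 0.5, half of any such difference is expected to carry over: 0.5 × 0.35 = ±0.17 SD in an unadjusted follow-up difference, against a target of 0.5.

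**The case against.** The best answer is that the article is silent on this and has not chosen wrongly. It is a condensed journal account, and the statistical analysis plan is not at hand. Model and covariates are commonly fixed there, and comparing scores over time, inside and across arms, could describe a group-by-time, change-score or covariate-adjusted analysis.

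Much of this stands. A reader might infer that the trial has decided to compare raw, unadjusted scores. The text does not say so and does not rule out a model that uses baseline. The t-test sample size is no proof either: leaving r out is a conservative planning choice and fits a later ANCOVA. A reader might also infer that the unadjusted result would be biased. It would not be, because chance imbalance is already reflected in its standard error; what is lost is efficiency and accuracy conditional on the imbalance that occurs.

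Nor can it be claimed that adjustment restores the power lost in controlling error over three primary outcomes. The article states no such correction. If an equal split of α were assumed (0.05/3 = 0.0167), unadjusted power per outcome would be about 66%, and ANCOVA would give about 70% at r = 0.3 and 79.8% at r = 0.5. It regains the planned 80% only from r of about 0.5 upwards.

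The objection does not dispose of the point. The article does print an analysis description, worded as what the analyses consist of, and its plain reading makes baseline a time point. The change-score reading does not rescue it: on the figures above, change scores are weaker than ANCOVA at each r shown, no better than an unadjusted comparison at r = 0.5, and worse at r = 0.3.

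**Conclusion.** The point holds as an avoidable loss of precision. Followed as written, the analysis does not commit to using a baseline score that exists for every randomised participant. The unadjusted comparison would still be valid, and the sample sizes of 128 and 183 need no change.

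The gain from adjusting is about 4, 10 or 17 percentage points of power at r = 0.3, 0.5 or 0.7, with 64 completers per arm and d = 0.5. It could therefore be modest or large. The figures rest on an assumed r, applied alike to three outcomes and two follow-up times, and on a linear relation, which may fit AUDIT-C less well if many participants do not yet drink. This is worth changing before the data are analysed, but it does not threaten the trial's validity.

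**What to change.** State in the Analyses section, or confirm in the statistical analysis plan, that:

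- the main between-group estimate for each primary outcome at follow-up is adjusted for that outcome's own baseline score, by ANCOVA or by a mixed model with baseline as a covariate;
- it is reported as an adjusted mean difference with a 95% CI, and Cohen's d is derived from that difference, with its denominator named;
- within-group changes and the comparison of arms at baseline are descriptive only.

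Further covariates and the choice of SD for d are for the trial team, and nothing in the article dictates them. The cost is one paragraph of text, with no new data and no change to the recruitment target. If the analysis plan already specifies such a model, the article's sentence only needs to say so.

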### Ethics

This study has been approved by The Regional Ethical Review Board at the Karolinska Institutet (registration nr. 2011/1648-31/5).

## Discussion

The study described herein involves the web-ICAIP, a therapist assisted web-based self-management intervention targeted at adolescents aged between 15 and 19 years, having at least one parent with alcohol problems. The efficacy of this intervention program will be assessed using a RCT study design with two conditions, where one group have access to the web-ICAIP and the other group consists of a waiting list control group. The two experimental conditions will be compared with each other.

### Strengths and limitations

The present study has a number of strengths. First, the web-ICAIP is a web-based intervention program, and it appears as if the Internet is a particularly promising way to provide support to adolescents growing up with parents having alcohol problems, since it offers an anonymous means of communicating and makes intervention programs readily accessible [22]. Additionally, this program is one of the first web-based interventions aimed at this target group and may prove to be an effective strategy to deliver, not only therapist assisted self-management programs, but also other forms of support such as online support groups. Another strength is that the web-ICAIP involves personalized tailored feedback, in the form of pre-written automatic messages and therapist-written personalized feedback, both of which has proven to be important components in web-based interventions aimed at adolescents [45]. Finally, this study attempts to evaluate the efficacy of web-ICAIP using a RCT study design, which is considered to be the strongest experimental design with regards to allocation bias, thus increasing the probability that participant characteristics in the two conditions are similar.

There are also possible limitations to this study. First, the web-ICAIP will be delivered *via *the Drugsmart web portal, which has existed for more than 10 years and since 2009 also includes information and various activities for children growing up with substance abusing parents. This precludes closing down this website during the study period and both the intervention group and the waiting list control group will subsequently have access to Drugsmart. Although the effects of Drugsmart have not been evaluated, it is possible that visitors may be affected, thus threatening the internal validity. We will therefore include questions in the follow-up assessment about the participants' activities on this website. A further limitation is that the participants will be screened for having parents with alcohol problems using the CAST-6 instrument which has not been validated in a Swedish setting. Yet another limitation concerns selection bias and the external validity. Our intention is to recruit study participants *via *Drugsmart and other related websites. It is therefore possible that the majority of the study population can be classified as "information-seeking" adolescents, who may have different personality traits relative the general population. In addition, since an inclusion criterion is to have readily accessibility to a computer and the Internet, it is possible that study participants belonging to a lower socioeconomic class will be underrepresented. Finally, this study is powered to detect a medium effect size. However, if the anticipated effect size is too large the study is under-powered. Similarly, the study may also be under-powered if the attrition rate turns out to be larger than 30%, which is the figure that has been accounted for in our theoretical sample size calculation.

